### Recruitment

During the surgical preadmission visit, a member of the patient’s circle of care (e.g., surgeon, anesthesiologist, nurse) will invite all elective cardiac surgical patients meeting eligibility criteria to speak with a research coordinator about potential participation in the study. Interested patients will meet with a research coordinator who will provide study information and, where appropriate, obtain written informed consent prior to the scheduled surgical procedure. Thereafter, the research coordinator will contact the hospital blood bank to ensure the availability of adequate supplies of both types of platelets for each patient on the day of surgery (as randomization will only occur on the day of surgery but ABO-identical cold-stored platelets will be prepared a minimum of 24 h prior to the scheduled surgery—see “Randomization/assignment of interventions” section below).

### Randomization/assignment of interventions

Recruited patients will only be randomized on the day of surgery if the clinical team places an order with the blood bank for platelet transfusion to treat active bleeding during the first 6 h after termination of CPB, and both platelet types are available (Fig. 1). When the platelet order is received, the blood bank technologist or assigned research coordinator will confirm the patient has consented to the study and is enrolled in the trial. The patient will then be randomized and the assigned product will be released [18, 24].

Patients will be randomly assigned (1:1 ratio) to study groups on the day of surgery using a permuted block, stratified (by center) allocation scheme prepared by a biostatistician not involved in the trial. Sequentially numbered sealed envelopes based on the randomization lists will be provided to the blood banks that will be providing the platelet product. This process, which has been successfully used in previous similar studies [25–28], has the advantage of allowing the technologists or coordinators to randomize patients as soon as the order is received without delaying therapy. The spot in the randomization list will not be reused if the patient assigned to it does not receive the platelet product. Once the order for the first platelet product is received and eligibility has been confirmed, the blood bank technologist will open the randomization envelope, and prepare and release the assigned platelet product in tamper-proof, temperature-stable containers that have been validated for this purpose and will be identical for each study arm. To maintain blinding, thermal gloves will be released by the blood bank for product handling and the product label (containing collection and expiration dates and type of platelet) will be obscured.

### Interventions

Patients randomized to the room temperature platelet (RTP) group will receive ABO-identical, pathogen-reduced via INTERCEPT [29], buffy-coat platelets in platelet additive solution maintained at 22 °C for up to 7 days, as per the current standard of care.

Patients randomized to the delayed cold-stored platelet (DCSP) group will receive up to two doses of ABO-identical, pathogen reduced via INTERCEPT, buffy-coat platelets in platelet additive solution maintained at 22 °C for up to 4 days (with agitation) then placed in cold-storage (at 1–6 °C, without agitation) for a minimum of 24 h, with expiration at 14 days after collection.

The duration of treatment is from the initiation of the first platelet transfusion up to 24 h after CPB or receipt of two doses of the product, whichever occurs first. There will be no other changes to participants’ pre-and post-operative management.

The clinical team will then administer the platelets only if the following criteria are met: [23, 30] (a) bleeding is severe enough to necessitate treatment (Bleeding Severity Scale Moderate or higher [31] or chest tube output ≥ 200 mL/h for any 1 h or ≥ 2 mL/kg/h for 2 consecutive hours in the first 6 postoperative hours [32]; (b) heparin is adequately reversed (confirmed by the return of post-protamine activated clotting time [ACT] to within 15% of baseline ACT); and (c) presence of thrombocytopenia (total platelet count < 100,000 × 10^6^) or platelet dysfunction (functioning platelet count < 75,000 × 10^6^ in response to collagen activation, as measured by the point-of-care platelet function assay PlateletWorks currently in use at both sites). Patients can also be treated irrespective of the platelet count or function if bleeding is deemed to be life-threatening, in accordance with institutional coagulation management algorithms for massive bleeding previously validated by our group [23]. Once the decision is made to administer platelets, the administering clinician will put on the insulated gloves provided, retrieve the product from its sealed temperature-controlled container, carry out routine checks, and administer according to usual care including in-line filtration tubing (170–260 µm) primed with normal saline.

If a second platelet order is received during the first 24 h after the termination of CPB, the blood bank will prepare and release the correct product (according to group allocation) as per the first unit (in a tamper-proof container along with insulated gloves). To minimize the theoretical thromboembolic risks of cold-stored platelets, if patients require more than two doses of platelets (expected to occur in < 3% of patients, based on data from a recent trial by our group [23]) or require therapy after the 24-h treatment period has elapsed, the blood bank will prepare and release room temperature platelets for both groups. Additional doses of platelets can be administered if there is at least moderate bleeding [31] and other coagulation abnormalities have been addressed as per the standardized coagulation management protocol [23].

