### Outcomes

#### Primary feasibility endpoints

Adequate recruitment (defined as ≥ 15% of eligible patients enrolled per center per month to target consistent levels of enrollment) [33]Adequate cold-stored platelet supply (defined as appropriate product available at the time of surgery for ≥ 90% of patients randomized to the delayed cold-stored platelet group).Adequate clinician adherence to randomization assignment (defined as > 90% of all patients being administered the assigned product).

Recruitment and protocol adherence are key common progression criteria for internal pilots of efficient RCTs and ensuring adequate supply of cold-stored platelets is a critical metric for ensuring feasibility of the definitive trial. If all primary feasibility endpoints are met, we will proceed with the larger trial. If 1–2 of 3 feasibility endpoints are met, we will decide if the trial is feasible with modifications to the protocol addressing the specific deficiencies in trial design identified in the pilot. The trial will be considered infeasible if all primary feasibility endpoints fall short of their targets and can not be addressed with modifications to the study protocol. We will hold an investigator meeting to examine the type and number of major deviations, and to define protocol changes required based on the feasibility outcomes.

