### Determination of sample size

This pilot study will include 50 randomized patients, which, accounting for patients who are randomized but not treated and patients who withdraw in both arms, is expected to provide at least 44 evaluable patients, with 22 in each arm. This sample size of 50 patients allows for sufficiently precise estimates of feasibility outcomes [37] in a reasonable timeline. If fewer than 10% (< 5 patients) receive the incorrect product or receive no product, the upper one-sided 95% confidence limit for this percentage will be ≤ 17.3%. In the 25 patients assigned to cold-stored platelets, if at least 90% have product available, the lower confidence limit will be ≥ 77.7%.

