### Statistical analysis

For the statistical analysis of the efficacy parameters, the following analysis sets will be considered:

The intention to treat (ITT) population: all randomized patients who receive at least a whole or parts of an IMP dose, irrespective of the number of IMP doses received. We anticipate that ≥ 90% of randomized patients will receive the first dose of IMP. Should a patient receive IMP that is not in concordance with the randomization schedule, the treatment group will be defined according to the randomization (rather than the actual treatment received). The primary outcome and mortality for non-consenting patients will be collected from as many sites as possible, as permitted by the local REB.

The per-protocol (PP) population: all patients in the ITT sample, excluding patients with major protocol deviations. Patients meeting any of the following criteria will be excluded.Patients who do not receive at least 80% of the first platelet dose to which they were randomizedPatients receiving treatment not in concordance with the randomization schedulePatients who significantly violate inclusion/exclusion criteria (e.g., did not have cardiac surgery with CPB, randomized after POD-3, etc.)

The restricted safety population (safety analysis set): all patients who receive at least one whole or parts of the first platelet dose (i.e., the ITT population).

A final decision about the classification of protocol deviations as major and minor and their consequences regarding the assignment of patients to analysis populations will be made during the blinded data review meeting prior to unblinding for the final analyses by the lead PI.

The ITT analysis sample is considered the primary sample for analysis of the primary endpoint. The evaluation of the primary endpoint will additionally be performed for the PP sample.

The data will be analyzed using protocols established for safeguarding privacy and confidentiality. These include password-protected computers, locked file cabinets for hardcopies, and no public discussion of individual cases. There will be no linkages to other datasets, and no disclosures of person identifiers. Reports will present aggregate statistics only.

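### Patients left untreated because the protocol's own treatment criteria are not met count as misses on the clinician-adherence endpoint, and five of 50 are enough to miss it

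*Protocol article*

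**What the plan says.** All references are to the Protocol article.

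- **Trigger (Randomization/assignment of interventions).** A consented patient is randomised "if the clinical team places an order with the blood bank for platelet transfusion to treat active bleeding during the first 6 h" after bypass, provided both products are available. On receiving the order, the blood bank technologist or coordinator "will confirm the patient has consented to the study and is enrolled in the trial". Then: "The patient will then be randomized and the assigned product will be released". The next paragraph repeats the sequence: "the blood bank technologist will open the randomization envelope, and prepare and release the assigned platelet product". The list position of a patient who is not given product is not used again.
- **Treatment criteria (Interventions).** "The clinical team will then administer the platelets only if the following criteria are met". The criteria cover bleeding severity, heparin reversal, and low platelet count or function. Life-threatening bleeding waives the platelet count or function criterion.
- **Endpoint (Primary feasibility endpoints).** "Adequate clinician adherence to randomization assignment (defined as > 90% of all patients being administered the assigned product").
- **Counting rule (Determination of sample size).** "If fewer than 10% (< 5 patients) receive the incorrect product or receive no product", an upper one-sided 95% limit of at most 17.3% is claimed. The same section expects at least 44 evaluable patients of 50, after allowing for randomised patients who are not treated and for withdrawals.
- **Expected delivery (Statistical analysis).** "We anticipate that ≥ 90% of randomized patients will receive the first dose of IMP". Feasibility decisions compare point estimates with the targets.

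**The concern.** The endpoint is labelled as clinician adherence to the randomised assignment, but it is scored as delivery of the assigned product for any reason. Between randomisation and delivery stands a rule that obliges the team to withhold the product in some patients. If bleeding settles after the order, or the platelet result is above the threshold and bleeding is not life-threatening, the clinician who withholds the product has followed the protocol. That patient still counts as a miss, in the same category as a patient given the wrong product. No section exempts the case.

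Adherence is one of three progression criteria. A shortfall made up of protocol-compliant non-treatment would point the investigators towards clinician behaviour or product issue, when the cause is how often the criteria are unmet once an order has been placed. These causes call for different remedies.

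**Working it through.** **1. Confirm the counting rule from the plan's own figure.** Fewer than 5 of 50 means at most 4. The exact (Clopper-Pearson) one-sided 95% upper limit for x = 4, n = 50 solves P(X ≤ 4 | 50, p_U) = 0.05. This gives p_U = the 0.95 quantile of Beta(x + 1, n − x) = Beta(5, 46) = 17.38%, against the stated 17.3% (agreement if truncated). The denominator is therefore all 50 randomised patients, with wrong product and no product counted together.

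**2. Find where the target is missed.** More than 90% of 50 is more than 45, so at least 46 patients must be given the assigned product.

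| Not given assigned product | Delivered | Percentage | > 90%? |
|---|---|---|---|
| 4 | 46/50 | 92.0% | yes |
| 5 | 45/50 | 90.0% | no |
| 6 | 44/50 | 88.0% | no |

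The plan anticipates that at least 90% will be treated, while the target is strictly above 90%. At exactly 90% treated, the plan's expectation is met and its target is missed.

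**3. Chance of a miss with no clinician error.** Let p be the share of randomised patients correctly left untreated because the criteria are unmet. The documents do not give p, so a range is assumed. With patients treated as independent,

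P(miss) = P(X ≥ 5) = 1 − Σ_{k=0}^{4} C(50,k) p^k (1 − p)^(50−k).

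For p = 4%: 1 − (0.130 + 0.271 + 0.276 + 0.184 + 0.090) = 1 − 0.951 = 0.049.

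| Assumed p | P(miss) |
|---|---|
| 2% | 0.3% |
| 4% | 4.9% |
| 5% | 10.4% |
| 6% | 17.9% |
| 8% | 37.1% |
| 10% | 56.9% |

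The last row lies at the edge of the plan's expectation for all causes of non-treatment together. If true clinician error of 2% (also assumed) is added, the total at p = 4% is 6% and the chance of a miss rises from 4.9% to 17.9%.

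**4. Effect of scoring only what clinicians control.** Remove the patients left untreated because the criteria were unmet. Five such patients then give 45/45 and six give 44/44, both 100%. The tolerance for real errors does not loosen. Passing requires errors m < 0.1 × n, and for any n from 41 (m < 4.1) to 50 (m < 5) the largest m allowed is 4, the same as now.

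**The case against.** **The sequence is deliberate.** The protocol says that randomising on the order avoids delaying therapy and that the process worked in earlier similar trials. This stands. A reader might infer that the envelope should be opened only after the treatment criteria are confirmed. The documents do not support that: the reason for the sequence is stated, and an earlier check could not catch a patient whose bleeding settles after the order.

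**Misses can be explained.** A reader might infer that a miss could not be attributed to a cause. That goes too far. The Blinding section requires the reason for any returned dose to be recorded, and the endpoints section provides an investigator meeting on major deviations. What remains is that these data play no part in the endpoint definition.

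**The rate may be low.** The team that orders the platelets also applies the criteria, and orders are for active bleeding, so a small p is plausible. At 2% the problem is negligible. The allowance of 6 losses in 50 (12%) should not be read as p: it includes withdrawals, and 44 is a minimum. The corresponding 73% chance of a miss is therefore not supported. The expectation of at least 90% treated is likewise a floor for all causes, so 57% is an edge case and not a forecast.

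**Other readings of the text.** The randomisation section also requires eligibility to be confirmed before the envelope is opened, which could be taken to include the treatment criteria. However, the checks it names are consent and enrolment, and the Interventions section places the criteria after release. Table 1 does not settle the order: it lists randomisation and treatment criteria in separate rows but under the same column.

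**Counting every untreated patient is conservative.** As a measure of trial efficiency this is defensible, and it is a good reason to keep reporting that rate. It does not justify calling the rate clinician adherence.

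**Conclusion.** The point holds as a fault in how one progression criterion is scored. On the text, protocol-compliant non-treatment counts as clinician non-adherence, and five such patients of 50 miss the target without any clinician error. The probability of that depends on an unstated rate: about 0.3% at 2%, 5% at 4%, 18% at 6%, 37% at 8% and 57% at 10%, assuming independent patients and perfect clinician adherence.

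A reader might take a miss to stop the programme. It does not. With one or two of the three endpoints met, the investigators decide on feasibility with modifications, and a second pilot is considered only if those are significant. Infeasibility requires all three to fall short without a remedy. The consequence is a misleading signal to that review. The change is worth making before data are collected, but the point does not undermine the design.

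**What to change.** Leave the randomisation sequence and the treatment criteria unchanged, and change the scoring.

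1. Define non-adherence as either a wrong product given, or the assigned product not given although the criteria in the Interventions section (or the life-threatening exception) were met. Determine criteria status from the recorded laboratory and bleeding data and the return reasons.
2. Take patients who were randomised, did not meet the criteria and were not treated out of the adherence denominator, and report their number separately.
3. Report the share of all randomised patients who were given the assigned product alongside, as a measure of trial efficiency. Make the precision statement in the sample size section say which of the two rates it describes.

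The cost is a change of endpoint wording and one extra tabulation, mostly from data already planned. The downside is a slightly smaller adherence denominator that depends on documented criteria status, and so partly on records made by the clinicians being assessed. Keeping the all-randomised rate in the report guards against that.

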### Blinding

This will be a blinded randomized trial, with clinical personnel, patients, family members, and outcome assessors blinded to group allocation. Given that the platelets will be different temperatures (but identical in appearance), an unblinded blood bank technologist, who will not have access to the collected study data, will blind the platelets by placing them in an insulated tamper-proof container accompanied by a pair of disposable insulated gloves. Labels on the product indicating different product codes or revealing an extended date of expiration which may result in unblinding will be concealed. The clinician(s) directly handling the product at the time of transfusion will wear insulated gloves to prevent unblinding (simulations have shown this to be an effective strategy). To maintain blinding, the specific type of product administered will not be recorded in the chart. If any of the product doses are returned to the blood bank, the reason for the return and the status of the seal on the tamper-sealed container will be recorded by the technologist. Outcomes are objective and adjudicators will all be blinded, with an independent adjudication committee used for the main trial. Unblinding is permissible when septic, thromboembolic, or other SAEs occur. Under these circumstances, the Principal Investigator will unblind the patient and the clinical team by contacting the unblinded blood bank technician to reveal a patient’s allocated intervention. All episodes of inadvertent unblinding by the clinical team will be recorded as deviations.

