### Harms

The condition of the patient will be monitored throughout the study. At each visit, whether scheduled or unscheduled, Adverse Events (AEs) will be elicited using a standard non-leading question. In addition, the Investigator will check the patient records for any documented event. Any AE that occurs during the study will be noted in detail on the appropriate pages of the CRF. The Investigator will grade the severity of all AEs (mild, moderate, or severe), the seriousness (non-serious or serious), and the likelihood that they were related to the administered product (causality). The investigator will also assess the expectedness of each (expected or unexpected). The Investigator will provide detailed information about any abnormalities and about the nature of and reasons for any action taken as well as any other observations or comments that may be useful for the interpretation and understanding of an AE. Importantly, for any AE thought to be related to platelet transfusion, local policies for notifying institutional Blood Banks, Canadian Blood Services, the Transfusion Transmitted Injuries Surveillance System, and the Public Health Agency of Canada will be followed. Transfusion reactions will be classified and graded by the International Society of Blood Transfusion haemovigilance criteria (Standardized definitions | The International Society of Blood Transfusion (ISBT) (isbtweb.org)).

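### Any SAE permits the Principal Investigator to learn and disclose the allocation, yet causality and the analysis populations are judged by investigators with no stated protection against that knowledge

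*Protocol article*

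**What the plan says.** Four places in the protocol article bear on this point.

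- **Blinding, who is blinded.** The trial is described as "with clinical personnel, patients, family members, and outcome assessors blinded to group allocation".
- **Blinding, code breaks.** "Unblinding is permissible when septic, thromboembolic, or other SAEs occur". When this happens, "the Principal Investigator will unblind the patient and the clinical team by contacting the unblinded blood bank technician". The only unblinding that this section says will be recorded as a deviation is inadvertent unblinding by the clinical team. It also states: "Outcomes are objective and adjudicators will all be blinded, with an independent adjudication committee used for the main trial".
- **Statistical analysis.** The final decision on which deviations are major or minor, and what that means for the analysis populations, "will be made during the blinded data review meeting prior to unblinding for the final analyses by the lead PI".
- **Harms.** The Investigator grades every AE for severity, seriousness and expectedness, and also judges "the likelihood that they were related to the administered product (causality").

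The Outcome assessment section has blinded staff collect all outcomes from the medical record except the EQ-5D-5L, which a research assistant collects by telephone at POD-30.

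**The concern.** The stated trigger is the occurrence of an SAE of any kind. The rule does not say that the allocation must be needed for the patient's care. Code breaks would therefore fall among the patients with safety events, and the allocation passes through an investigator.

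Two later judgements assume that this knowledge is absent. One is the review that settles deviations and analysis populations. The other is the grading of the event itself, including its relation to the product. If both can be made with the allocation known, they can lean in either direction without anyone intending it. Two further outcomes are exposed once clinicians and patients know the allocation: blood components ordered after an early code break, and the patient's own quality-of-life report.

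This would matter little if the data stopped at a feasibility report. However, the Design and Statistical analysis sections provide for pilot outcome data, safety included, to enter the definitive trial's dataset. Judgements made after disclosure cannot be made blind again later.

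**Working it through.** The plan states no figure on this point, so the check is a comparison of its sections.

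**1. Who learns the allocation?** Under Blinding, the Principal Investigator, the patient and the clinical team.

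**2. Who decides the populations?** Under Statistical analysis, the closing phrase about the lead PI most naturally names the person who makes the decision. There are three readings:

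| Reading | Consequence |
|---|---|
| The PI who breaks the code is the lead PI | The review is not blinded for any patient whose code was broken |
| Each site's PI breaks the code (there are two sites) | The overlap remains at the lead PI's own site only |
| The phrase attaches to the final unblinding, not to the decision | The decision-maker is not stated, and nothing excludes a person who holds allocations |

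No reading gives the assurance that the word blinded suggests.

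**3. How much discretion is there?** Two of the listed per-protocol exclusions are largely factual: less than 80% of the first dose, and treatment that differs from allocation. The third, significant violation of eligibility, is open-ended and needs judgement, as does the major/minor classification itself.

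**4. In what order are events graded?** Harms gives grading to the Investigator. Neither Harms nor Blinding says that grading precedes disclosure. The independent adjudication committee is mentioned for the main trial.

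**5. Which outcomes can move?**

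| Item | Exposed after a code break? |
|---|---|
| Feasibility endpoints | No |
| Death | No |
| Occurrence of the SAE that prompted the break | No, it has already happened |
| AE severity and causality | Yes, if graded after disclosure |
| Major-deviation calls | Yes, where discretionary |
| Blood components transfused | Yes, if the break comes early; ordering is a clinician's decision |
| POD-30 EQ-5D-5L | Yes, it is self-reported by a patient who may know the allocation |

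**6. Is the situation likely to arise?** The article gives no SAE rate. With N = 50 randomized patients (Determination of sample size), independent patients and an assumed rate p, the chance that at least one patient meets the trigger is 1 − (1 − p)^50.

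- p = 5%: 1 − 0.95^50 = 0.92
- p = 10%: 1 − 0.90^50 = 0.995
- p = 20% to 40%: above 0.999

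This is the chance that the permission becomes available at least once. It is not a count of unblinded patients and not a measure of bias.

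**The case against.** The strongest reply is that this is a feasibility pilot that makes no formal inference on clinical outcomes. ITT is the primary sample and per-protocol is additional. Adjudicators and record abstractors are stated to be blinded. A data review before treatment codes are released is a standard step, and isolated code breaks do not make its name false. A condensed article may also leave code-break procedures to the full protocol. Much of this stands, and it limits the consequences. It does not remove the point, because the article states a rule open to any SAE and does not square it with its own account of who judges blind.

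A reader might infer more than the text supports:

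- **That coordinators open envelopes.** The Randomization section does speak of "allowing the technologists or coordinators to randomize patients as soon as the order is received", but it then says that the blood bank technologist opens the envelope.
- **That Table 1 schedules unblinding before POD-30.** The unblinding row is also marked at each platelet administration, where scheduled unblinding would defeat the design. It reads as a record of events. It therefore offers some logging, although what it captures is not stated.
- **That a large, known share of patients will be unblinded.** The SAE rate would be assumed, and it would count patients eligible for a permitted act.
- **That the whole safety comparison loses its blind.** No listed safety outcome is defined by relatedness to the product.
- **That product choice is open to influence.** The blood bank releases the second dose by allocation, and room temperature platelets for everyone after that.

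**Conclusion.** The point holds in a limited form. The Blinding, Statistical analysis and Harms sections do not fit together: the route for individual code breaks can place allocations with the person who settles the analysis populations and with those who judge severity and causality. The overlap on populations is complete if the lead PI breaks all codes, and partial if site PIs do. It rests on reading the lead PI as the decision-maker; on the alternative reading, the decision-maker is unstated.

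No bias can be quantified from the document. The pilot's go/no-go decision on feasibility is not threatened. The exposure lies in the four items marked as exposed above, and it gains weight because pilot outcome data may be carried into the definitive trial. A change in wording is worthwhile, and it is needed before recruitment because the order of judgement and disclosure cannot be restored afterwards.

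**What to change.** Reconcile the three sections as follows.

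1. **Grade first.** The Investigator records severity and causality before any allocation is disclosed. This must not delay a disclosure that the investigators judge clinically necessary; in that case, mark the grading as made after disclosure.
2. **Separate the decision-maker.** Deviations and analysis populations are decided by someone who holds no individual allocations, and the text names that role.
3. **Log every code break.** Record permitted and inadvertent breaks alike, with date and time relative to the end of CPB and to the grading and EQ-5D-5L entries. Report counts by arm.

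The grounds for unblinding are a clinical matter. The investigators should state them themselves, so that the Blinding section and the rest of the article agree.

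The cost is a few sentences, one short form, and a different decision-maker for deviations. Sample size, treatment and visits do not change.
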